### Participants

Participants will be service users currently in treatment for SUD who meet the following inclusion criteria: (i) aged 18 years or above, (ii) experiencing problem alcohol and/or drug use for ≥ 12 months requiring treatment, as determined by clinical personnel at the service, (iii) willing to comply with an eight-week treatment program for problem alcohol and/or drug use, (iv) willing to provide outcome measures post-treatment, and at three and six-months follow-up, (v) able to read, write and communicate in the English language, (vi) willing and able to access an internet enabled device for the eight-week treatment period, (vii) willing and able to give informed consent for participation in the study, and capable of understanding and complying with protocol requirements.

Exclusion criteria are as follows: (i) under 18 years of age, (ii) participation in any other alcohol and/or drug related clinical studies within 12 months prior to date of consent, (iii) detention under the Mental Health Act, (iv) clinically significant intellectual or developmental disability which may impair ability to engage with BFO and/or complete the necessary assessment measures included in the methodology, (v) pregnancy (as self-reported), (vi) previous use of BFO to address drug or alcohol use within the past 12-months.

The projected sample size will require 61 evaluable participants in each of the two treatment groups (interventional and control) to achieve enough observed power (assuming an observed power of 0.80 with α = 0.05) with an allowance of 50% attrition at three and six-months follow-up, in order to detect a medium effect size (d ≤ 0.50). Therefore, to obtain a total of 122 evaluable participants, it is estimated that a total of 183 participants will need to be recruited and screened. These estimations have been based on previous alcohol and drug studies size samples [8], some of which have used longitudinal statistical analyses.

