Interim analyses will be performed on the first 30 participants of each group to have completed the three- and six-months follow-up assessments after treatment completion. The data will be subjected to ANOVA and ANCOVA. Changes over time in psychometric assessment scores within each group will be conducted using Wilcoxon Signed Ranks Tests, assuming data are non-normally distributed. If following the interim analysis, a significant difference in outcomes is detected between the groups, either the sample size will be recalculated or recruitment will be discontinued, depending on the statistical power obtained.

Sub-group analyses will be conducted to examine the influence of sociodemographic variables such as age and gender, and clinical characteristics such as primary problem substance and clinically relevant depression and anxiety, on outcomes. Sub-group analyses will be conducted using ANOVA, ANCOVA and regression.

Intention-to-treat (ITT) principles will be followed, with data from all randomised participants being included in these analyses. Mixed effect models will be used to handle missing data by maximum likelihood estimation, which uses all available data from randomised participants and has been demonstrated to minimise bias more effectively than other approaches [46]. A number of strategies will be employed to maximize follow-up and prevent missing data as far as possible. These will include the study team contacting participants directly to chase-up incomplete assessments and working closely with clinical staff to contact those participants who cannot be contacted by the study team directly—reasons for missing data and drop-out will be recorded where this information is available. Additionally, non-randomised, observational, per-protocol comparative analyses will be conducted using data only from participants who fulfilled all protocol requirements in terms of eligibility, intervention receipt, and outcome assessment completion, in order to ascertain effects from BFO under ideal conditions.

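### The interim rule can stop recruitment or resize the trial on a significant difference with no boundary, outcome or time point fixed, so the 5% error rate is not protected

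*Protocol article*

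**What the plan says.** All of the interim text is in the protocol article under Data analysis and management.

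- **Who is analysed:** "Interim analyses will be performed on the first 30 participants of each group to have completed the three- and six-months follow-up assessments".
- **How:** "The data will be subjected to ANOVA and ANCOVA", with within-group Wilcoxon tests alongside.
- **Trigger and action:** "If following the interim analysis, a significant difference in outcomes is detected between the groups, either the sample size will be recalculated" or recruitment is discontinued, the choice depending on the power obtained.

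The only level that can apply to a between-group comparison is in the sample-size paragraph under Participants: "assuming an observed power of 0.80 with α = 0.05". The stricter level of 0.001 under Data analysis and management belongs to the within-group Wilcoxon tests. The same section later says that all randomised participants enter the intention-to-treat analyses and that mixed models handle missing data.

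Under Outcomes, the primary outcome is two questions (days of use in the past week, and amount per day), each assessed at end of treatment, three months and six months.

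**The concern.** The article does more than mention an interim look. It fixes the sample, the trigger and the action, and as written these have four weaknesses.

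1. A significant difference can end recruitment, but nothing says at what level, and no allowance is made at the final analysis.
2. The trigger refers to outcomes in the plural. Two questions at three post-baseline times already give six primary comparisons, and there are four secondary scales besides.
3. The choice between stopping and resizing rests on power computed from the interim result. That is a function of the p-value and adds no independent criterion.
4. The first completers are a selected set when half of participants may be lost. The Discussion expects the check-in calls, which only the intervention arm receives, to help retention, so completers could also differ between arms.

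At stake are the false-positive rate of the trial and the size of the effect it reports if it stops early.

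**Working it through.** **Inputs from the article.** α = 0.05 (two-sided assumed, as the article does not say), power 0.80, d = 0.50 (printed with a ≤ sign), 61 evaluable per arm, 183 recruited, 50% attrition allowed for, interim at 30 per arm.

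**Reproducing the plan's figure.** n per arm = 2(1.960 + 0.842)²/0.50² = 62.8, so 63. The stated 61 is close; its power is 0.79 by the normal approximation and 0.78 by the t-test. The final n could also be about 46 per arm, since half of 183 is 91.5.

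**Two looks at 0.05, one outcome.** Under no effect, the interim and final z-statistics are bivariate normal with correlation √(n₁/n₂). The type I error is 1 − P(|Z₁| < 1.96 and |Z₂| < 1.96), if a significant interim counts as success.

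| Final n per arm | n₁/n₂ | Type I error |
|---|---|---|
| 46 | 0.652 | 7.8% |
| 61 | 0.492 | 8.3% |
| 122 | 0.246 | 9.1% |

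**Six primary comparisons able to trigger.** By simulation at 30 and 61 per arm, with assumed correlations of 0.7 or 0.5 both between times and between questions, the error over both looks is about 28% (0.7) to 34% (0.5). At a single look it is already about 18% to 22%, so much of this is multiplicity that would exist without an interim. The correlations are my assumption; the article gives none.

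**What observed power adds.** Observed power is approximately Φ(|z| − 1.96). At p = 0.05 this is 50%. Observed power of 80% means |z| = 1.96 + 0.84 = 2.80, that is p of about 0.005, or an observed d of 2.80 × √(2/30) = 0.72.

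**Other readings of the rule (one outcome, two-sided 0.05).**

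| Reading | Type I error |
|---|---|
| Stop only if observed power is at least 80%, otherwise go on to 61 per arm | 5.2% |
| Same stop, otherwise resize on the observed effect | 5.8% |
| Significant interim stops recruitment, but all enrolled are followed; final test at 45 to 61 per arm | 5.6% to 5.0% |
| Significant interim, no stop, enlarge to 122 per arm | just over 4% |

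In the third row, a final sample of only 40 per arm would give 6.0%.

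**Size of the estimate.** At 30 per arm the smallest significant observed d is t(0.975; 58 df) × √(2/30) = 2.002 × 0.258 = 0.517, above the design effect of 0.50. Interim power at d = 0.50 is 48% (t) or 49% (normal). The mean estimate among significant interims is d + s·φ(k)/(1 − Φ(k)), with s = √(2/30) = 0.258 and k = 1.96 − d/s. This gives 0.71 for true d = 0.50 and 0.65 for true d = 0.30.

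**Boundary.** Lan-DeMets O'Brien-Fleming spending at 30/61 = 0.492 spends 2[1 − Φ(1.96/√0.492)] = 0.0052 at the interim. The final level that brings the total to 0.05 is 0.048.

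**The case against.** The strongest reply is that 8.3% and 0.71 model a rule harsher than the one written. What stops is recruitment, not follow-up, and only in some cases. If the article's own 80% target were the power threshold, the rule would act as a boundary near p = 0.005, much like the one recommended here.

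Completing six-month follow-up takes about eight months, so many more people would have joined by the time of the interim. At 50% attrition, 60 completers imply about 120 randomised. If 183 were recruited evenly over the 24 months from May 2021 to May 2023 (an assumed pace), about 8 × 7.6 = 61 more would be enrolled by then, or about 181 in all. Stopping would then remove very little. This stands as a limit on the size of the problem. It does not repair the rule, because the article gives neither a power threshold nor a statement that those enrolled will be in the final analysis.

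Three further objections stand. Enlarging the trial after a significant interim does not by itself raise the error, so the fault lies with stopping and not with every resize. Any design overestimates among its significant results: a fixed trial of 61 per arm averages 0.57 when the true d is 0.50. Finally, a reader might infer that analysing completers contradicts the intention-to-treat sentence. It need not, because that sentence can be read as describing the final analysis.

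It can also be said that a condensed article leaves interim levels to the analysis plan. That would answer a bare mention of an interim look. Here the trigger and the action are already fixed, and a reader following them has only 0.05 to apply.

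**Conclusion.** The point holds as a defect in the stated rule. Its size depends on how the rule is carried out. The type I error is about 8.3% (7.8% with 46 per arm at the end) for one outcome, two-sided 0.05 at both looks and a significant interim taken as the result. It is about 5% to 6% under the milder readings, which the article does not state. The 28% to 34% figure applies only if all six primary comparisons can trigger the rule and depends on assumed correlations. That the level is unadjusted is itself inferred, from 0.05 being the only between-group level given.

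A reader might infer that the trial will run at 8% or more, or will report an effect some 40% too large. The documents do not support either as the expected result: 0.71 is an average over trials that stop and report at 30 per arm, and the article does not say that the interim estimate would be the final one. What they support is that nothing written prevents these outcomes. The use of early completers is a further risk of bias.

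**What to change.** Rewrite the interim paragraph as follows.

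- Name one primary outcome and one time point for the interim comparison.
- Include all randomised participants whose six-month visit is due, analysed with the mixed model already planned.
- Use a Lan-DeMets O'Brien-Fleming boundary: two-sided p below about 0.005 at 30 of 61 per arm and below about 0.048 at the end, recomputed if the information at the look differs.
- Let this boundary replace the clause that makes the decision depend on the power obtained.
- State that participants already enrolled when recruitment stops are followed and included in the final analysis.
- Base any sample-size recalculation on the pooled, arm-masked SD and attrition only.

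The cost is protocol wording and a slightly stricter final threshold, 0.048 in place of 0.05.

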Research around the efficacy of BFO has demonstrated significant reductions in substance use, substance dependence, depression and anxiety, and biopsychosocial impairment, and improvements in quality of life—these studies have been conducted with people using opiates [18], cannabis [19], alcohol [20] and methamphetamine [21]. BFO studies have also been conducted in multiple treatment settings, including eTherapy ‘dual diagnosis’ mental health services [22, 23] and in UK [24, 25] and US [21] prisons. Research has also indicated that users follow tailoring advice provided by the program [26] and has also demonstrated a ‘dose response’ [19, 25, 26]. Baseline clinical characteristics of individuals engaging with the program have been demonstrated to be associated with engagement and outcomes [18, 20, 27].

A significant barrier to accessing in-person SUD services since March 2020 has been the impact of societal lockdowns to curb transmission of ‘severe acute respiratory syndrome coronavirus-2’ (SAR-CoV-2), or ‘COVID-19’. Social isolation throughout the pandemic, a known risk factor for SUD [28], may not have only potentially increased the vulnerability of individuals already living with SUD, but also increased the numbers of people with SUD. Figures published by the charity Alcohol Change UK indicate that COVID-19 has had a detrimental effect on drinking habits in the UK, with one in five individuals reporting increased alcohol consumption after the lockdown measures were introduced—this represents 8.6 million adults [29]. Studies conducted during the pandemic indicate that this increased consumption is associated with greater depression, anxiety and stress [30].

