### Interventions

Participants in the intervention group will be encouraged to spend one-hour per week working on BFO for the eight-week treatment period. Online access to BFO is granted via the activation of an online account using a ‘service code’ provided by the study team. Participants must agree to a Terms and Conditions of Use when they activate their account, which is in accordance with the Participant Information Sheet and Informed Consent Form and conforms to the United Kingdom General Data Protection Regulation (GDPR).

Upon account activation, each participant will be required to complete a baseline assessment of their substance use and dependence, and their wider biopsychosocial functioning. Included in this assessment is the ‘Recovery Progression Measure’ RPM: [34, 35], which measures levels of functioning across six biopsychosocial domains. BFO then uses these data to populate a six-domain model (see Fig. 1), the ‘Lifestyle Balance Model’ LBM: [36]. The LBM acts as a clinical formulation to help the user understand the specific issues and domains of functioning that may be implicated in their substance use and provides access to the clinical content of the program (See Table 1).

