**Fig. 1 Fig1:**
[figure not shown]
The Lifestyle Balance Model

Based on RPM scores, each of the domains of the LBM are colored either green, amber, or red, indicating respectively, ‘little’, ‘moderate’ or ‘significant’ impairment. Tailoring advice then guides the user to complete clinical content of the program that is able to address the domains of their functioning in the LBM where they may be experiencing the greatest levels of impairment (amber and red domains of the LBM). Individuals are able to address these domains of functioning by completing the 12 main BCTs included in the program (see Table 1). Every two-weeks BFO prompts each user to complete a mandatory ‘Progress Check’ assessment, which is comprised of the same items as the baseline assessment. Alongside providing access to the BFO program, participants will receive fortnightly 15–20 min recovery check-in telephone calls from the SUD service—a total of four telephone calls during the treatment period. Phone calls will include questions relating to the participant’s understanding and perception of the content of BFO, their ability to practice and rehearse the skills they are learning from the program, and support needs.

**Table Tab1:** The 'behavioral change techniques' (BCTs) contained within Breaking Free Online

Content in Breaking Free Online	Description of strategy	Therapeutic approaches underpinning strategies	BCT taxonomy (V1) techniques (number in taxonomy)
Baseline and progress check assessments	Monitor behavior to provide feedback about progress towards goals; Encourage new behaviors via positive feedback	Goal setting; self-monitoring	Self-monitoring of behavior (2.3); Feedback on outcome(s) of behavior (2.7)
Lifestyle Balance Model	Generic formulation; Idiosyncratic formulation; Personalized feedback; Case formulation—understand the links between situations, thoughts, emotions, behaviors, physical sensations, and lifestyle	Node-link mapping (International Treatment Effectiveness Project (ITEP); Cognitive-behavioral therapy (CBT)	Information about antecedents (4.2); Information about health consequences (5.1); Salience of consequences (5.2); Information about social and environmental consequences (5.3); Information about emotional consequences (5.6)

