### Outcomes

Outcomes data will be collected via self-report, with participants completing an online assessment containing a series of standardized psychometric measures at Baseline, End of Treatment, and 3-month and 6-month follow up timepoints. Additionally, engagement data (time spent accessing the program, number of BCTs engaged with) will be collected automatically via the BFO backend database for those participants in the interventional arm.

The primary outcome will be self-reported substance use compared to baseline following treatment completion, and at three and six-months follow-up, which will be measured using the following questions:Weekly use of primary problem substance (i.e., ‘How many days in the past week did you use [primary substance]?’‘How much [primary substance] did you use each day?’)

Secondary outcomes will be measured at corresponding time points using the following standardized measures:Severity of Dependence Scale (SDS) [37, 38]: A five-item scale measuring severity of substance dependence—internal reliability: α = 0.81–0.90; test–retest reliability ICC = 0.89.Patient Health Questionnaire-4 (PHQ-4) [39]: A four-item scale that measures severity of depression and anxiety—internal reliability, α = 0.81.Five items (1, 2, 17, 18, 20) from the World Health Organization Quality of Life scale (WHOQoL-BREF) [40]—internal reliability of these five items, α = 0.84.Recovery Progression Measure (RPM) [34, 35]: A 36-item scale measuring functioning in six biopsychosocial domains functioning that are implicated in all SUDs and recovery from SUDs—internal consistency, α = 0.89; test–retest reliability, ICC = 0.73.

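### The per-protocol comparison filters the two arms unequally after randomisation, so it cannot deliver the causal effect of BFO that the plan asks of it

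*Protocol article*

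**What the plan says.** The Protocol article, Data analysis and management, puts ITT first: "Intention-to-treat (ITT) principles will be followed, with data from all randomised participants being included in these analyses". It then adds: "Additionally, non-randomised, observational, per-protocol comparative analyses will be conducted". Membership of the per-protocol set is defined as follows: "using data only from participants who fulfilled all protocol requirements in terms of eligibility, intervention receipt, and outcome assessment completion". The reason given for the analysis is: "in order to ascertain effects from BFO under ideal conditions".

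What counts as receipt differs by arm. Both arms get standard treatment (Relevant concomitant care), likely one or two sessions a week for eight weeks. For the BFO arm, Interventions adds two components. One is the program: "Participants in the intervention group will be encouraged to spend one-hour per week working on BFO for the eight-week treatment period". The other is the check-in calls: "a total of four telephone calls during the treatment period".

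Outcomes says that "engagement data (time spent accessing the program, number of BCTs engaged with) will be collected automatically via the BFO backend database", for the interventional arm only. The Introduction reports that "Baseline clinical characteristics of individuals engaging with the program have been demonstrated to be associated with engagement and outcomes".

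**The concern.** Restricting each arm to participants who received their intervention and completed assessments selects on behaviour after randomisation. That would matter little if the same kind of person were removed from both arms. Here it probably is not. A control qualifies by receiving standard treatment. A BFO participant must do that and also engage with a program whose use is only encouraged. The controls who would have engaged with BFO had they been offered it cannot be identified, because engagement is recorded in one arm only.

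The protocol supplies the remaining link, since it says that users' characteristics go with both engagement and outcome. The per-protocol difference then mixes any effect of BFO with a difference in prognosis, yet the plan gives that difference a causal purpose. At stake is a supplementary figure that could be read as what BFO achieves when used as intended.

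**Working it through.** **The plan's own figure.** The document gives no figure for the per-protocol analysis. The yardstick is the planned effect in Participants: d = 0.50 (printed as d ≤ 0.50), power 0.80, α = 0.05, 61 evaluable per arm. Two-sided, n = 2 × (1.96 + 0.84)² / 0.50² = 62.7, or 63 per arm. Power at 61 is 0.789. So 61 is reproduced closely, and 0.50 is a fair scale for judging the bias.

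**Assumed inputs.** The document gives neither a receipt rate nor a correlation. I assume:
- no true effect;
- a latent propensity to meet receipt, with correlation r to the outcome (higher is better), r = 0.2 to 0.3;
- 50% of the BFO arm kept by the receipt filter;
- 100%, 80% or 50% of controls kept by the receipt filter;
- 91 randomised per arm, taking the 183 in Participants as randomised 1:1.

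**Shift in the mean of those kept.** If the top share p is kept, the mean moves by r × λ, where λ = φ(c)/p and c = Φ⁻¹(1 − p).
- p = 0.5: c = 0, λ = 0.399/0.5 = 0.798.
- p = 0.8: c = −0.842, λ = 0.280/0.8 = 0.350.
- p = 1: λ = 0.

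**Spurious difference.** Bias = r × (λ for BFO − λ for control). With 80% of controls kept and r = 0.3, this is 0.3 × (0.798 − 0.350) = 0.134.

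**False-positive rate.** The variance among those kept is v = 1 − r²λ(λ − c). For the same case:
- v (BFO) = 1 − 0.09 × 0.637 = 0.943, with 45.5 kept;
- v (control) = 1 − 0.09 × 0.417 = 0.962, with 72.8 kept;
- SE = √(0.943/45.5 + 0.962/72.8) = 0.184, so bias/SE = 0.73;
- the chance that |z| exceeds 1.96 is about 0.11.

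| Controls kept by receipt | r | Spurious d | False positives, full outcome data | Same, 50% random attrition |
|---|---|---|---|---|
| 100% (no filter) | 0.2 | 0.16 | 14% | 10% |
| 100% (no filter) | 0.3 | 0.24 | 27% | 16% |
| 80% | 0.2 | 0.09 | 8% | 6% |
| 80% | 0.3 | 0.13 | 11% | 8% |
| 50% (equal filters) | 0.2 or 0.3 | 0 | 5% | 5% |
| any | 0 | 0 | 5% | 5% |

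Random attrition leaves the bias as it is and lowers the false-positive rate only because fewer participants remain.

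**Checks.** A simulation of 20,000 trials at 50% BFO receipt, unfiltered controls and r = 0.3 gave a bias of 0.239 and 26.4% rejections. With equal filters it gave 0 and 5%. Varying BFO receipt against unfiltered controls (r = 0.2 to 0.3), the bias is 0.23 to 0.35 at 30% receipt and 0.10 to 0.15 at 70%.

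**The case against.** The strongest reply is that the plan already says what this analysis is. It comes after ITT, it is additional, and it is called observational. That stands, and it means the trial's main inference is not touched. It does not rescue the purpose clause: the label concedes confounding, and the same sentence then asks for the effect of BFO.

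Three stronger readings are tempting, and the document does not support them.
- **Controls face no hurdle.** Eligibility, receipt and completion are required of all participants, and attending standard treatment over eight weeks is itself a filter. The hurdles are unequal, not one-sided. The unfiltered rows of the table are therefore an upper case for given r and BFO receipt, not the expected one.
- **The bias certainly favours BFO.** The Introduction's sentence on engagement and outcome gives no sign. Its mention of a dose response makes a favourable direction more likely but does not settle it. The Discussion says the calls are meant to improve retention in the BFO arm, which could make the completion filter milder there and push the other way. If r were negative, the sign of the bias would reverse.
- **Nothing in the plan addresses it.** Regression on baseline severity, mental health, functioning and quality of life is planned and could remove part of the measured confounding; the table models no such adjustment. But the text does not tie that regression to the per-protocol set, and unmeasured motivation would remain.

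It is also fair to say that a receipt threshold may be left to the full protocol or SAP. Its absence here is not part of the point.

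**Conclusion.** The point holds in a limited form. The per-protocol comparison is open to selection bias because receipt is a more demanding and largely voluntary condition in the BFO arm, and the protocol itself ties engagement to prognosis. It cannot establish what BFO does under ideal use. With 50% BFO receipt and r = 0.2 to 0.3, the spurious benefit is about a fifth to a quarter of the planned d of 0.50 if 80% of controls are kept (0.09/0.50 = 18%; 0.13/0.50 = 26%), and about a third to a half if controls are not filtered on receipt (0.16/0.50 = 32%; 0.24/0.50 = 48%). These sizes rest wholly on assumed receipt rates and correlations, and the bias vanishes if selection is equal or receipt is unrelated to outcome. A reader should not infer that the ITT result is compromised or that a false per-protocol benefit is to be expected. The defect is a causal aim attached to an analysis that cannot meet it.

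**What to change.** 1. Delete the purpose clause. Present the per-protocol table as descriptive and associational, adjusted for the baseline measures already collected.
2. Add a complier average causal effect analysis in all randomised participants, with allocation as the instrument and adjustment for baseline. Fix the definition of receipt before unblinding as any receipt of the package: BFO account activated or at least one check-in call.
3. Do not define receipt by a threshold of time or BCTs. Participants below it may still have had calls and some BFO. Allocation would then affect people classed as not having received it, and any benefit they gained would inflate the estimate.

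The cost is a paragraph of wording and one further analysis, using account data already held and a record of calls made. The interval will be wider: if controls have no access, the estimate and, approximately, its standard error are those of ITT divided by the share receiving the package, so at an assumed 70% the interval is about 1/0.70 = 1.43 times as wide. The analysis relies on the exclusion restriction (allocation acts only through the package) and on the same missing-data assumption as the ITT model. It estimates the effect of receiving the package at all, not of ideal use, which this design does not identify without stronger assumptions.
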